### 2.2. Participants

A convenience sample of HW and HC participants will be recruited to complete the study. Participants must provide written, informed consent before any study procedures occur. Eligibility criteria will differ across groups.

HW participants will consist of both registered and non-registered staff, including pharmacists, physiotherapists, occupational therapists, social workers, nurses, doctors, health care assistants, ward clerks, and domestic services staff. With an estimated drop-out rate of 25%, we will recruit up to 138 healthcare worker participants to ensure completion of 110 (55 per ward). Inclusion criteria for healthcare worker participants include (a) being employed in the clinical sites and (b) giving informed consent. Exclusion criteria include (a) working across both the intervention and control wards; (b) agency staff working across multiple wards; or (c) being a medical student, a nursing student, or an allied health student.

HC participants will consist of hospitalised patients and their visiting support persons. With an expected non-completion rate of 10%, we will recruit up to 165 participants to ensure completion of 150 (75 per ward with 25 per timepoint) to complete the study. Inclusion criteria for healthcare consumer participants include (a) ability to understand, read and write English; (b) capacity to give informed consent; (c) (for patients only) being ready for discharge—this is to allow patients to reflect on their experiences and interactions in a non-acute phase of their illness; and (d) (for support persons only) have been actively supporting the patient during their admission (i.e., visited patient at least once per week). Exclusion criteria include (a) being unable to give informed consent; (b) being under the age of 18 years; (c) (for patients only) not predicted to be discharged from the ward between the data collection periods; and (d) (for support persons only) have not been involved in regular support of the patient (i.e., visited less than once a week).

*Risk to participants.* To ensure any risk is minimal in the research, our study design was guided by the following considerations. (1) Appropriate research team member selection: the research team consists of researchers who have expertise in empathy, wellbeing, and coaching. (2) Incorporating self-regulation tools: healthcare worker participants undertaking the EmpEd will be asked to explore differences among people and examine their feelings and attitudes. These activities could raise emotional distress for some participants. To mitigate the risks, the immersion programme has embedded self-care and self-compassion components. (3) Research site selection: the two research sites were selected based on key characteristics—stable workforce, predictable patient population, and stable leadership—to minimise any potential risk to participants. (4) Participant eligibility and exclusion criteria: strict eligibility and exclusion criteria are applied to each potential participant before signing up to the study. (5) Access to workplace Employment Assistance Programme (EAP): if any potential risk should arise that a member of the healthcare team is concerned about, the DHB research team liaison, as well as the principal investigators will be consulted, and appropriate actions will be taken. Non-serious adverse events will be collected systematically during the research and recorded in the case report form.

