### 3.3. Sample Size Calculation

Two independent HW groups will be assessed across three time points. An estimated 55 staff in each group (110 total) is required to achieve at least 80% power to detect a difference in the outcome measures as a response to the intervention. Applying the Bonferroni correction, the significance level for each test is adjusted to α = 0.05/9 = 0.0056. To assess HCs, initial power calculations suggested that for each HC group, a sample size of 50 per group per timepoint in each ward (300 participants) would result in a confidence interval limit of ±0.139 or 13.9% on a result of 0.5 or 50%. However, we expect that it would be difficult to achieve a sample size of >25 per group. The validity assessment will guide decisions regarding whether combining the two HC groups (patients and support persons) into one HC group per ward per timepoint is advisable. This part of the study is subject to modification and treated as exploratory. Power calculations were conducted in G*Power Version 3.1.9.4 for Windows.

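### The healthcare worker recruitment ceiling of 138 is 110 × 1.25, not 110 / 0.75, so at the stated 25% drop-out it leaves about 103 completers rather than the required 110

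*Protocol article*

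**What the plan says.** Section 2.2 (Participants) sets the healthcare worker target: "With an estimated drop-out rate of 25%, we will recruit up to 138 healthcare worker participants to ensure completion of 110 (55 per ward"). Section 3.3 (Sample Size Calculation) shows where the 110 comes from: "An estimated 55 staff in each group (110 total) is required to achieve at least 80% power to detect a difference in the outcome measures". The per-test level is given there too: "the significance level for each test is adjusted to α = 0.05/9 = 0.0056". No effect size, standard deviation or test is named for this calculation.

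Section 2.3 (Procedure, data collection) leaves anyone who discontinues out of every analysis, so only completers count towards the 110.

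The healthcare consumer target in section 2.2 is built the same way: "we will recruit up to 165 participants to ensure completion of 150 (75 per ward with 25 per timepoint"), with an expected non-completion rate of 10%. Section 3.3 describes the consumer part as exploratory and open to change.

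**The concern.** A drop-out rate is a share of the people enrolled. To finish with n completers when a fraction d is lost, one must enrol n / (1 − d). The two targets in section 2.2 look like n × (1 + d), which is always smaller. The gap widens with d, so it is visible at 25% and barely so at 10%.

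The phrase "we will recruit up to 138 healthcare worker participants" makes 138 an upper limit. The plan therefore caps recruitment below what its own loss rate calls for, while saying that the cap will secure the completers on which the power statement depends. If drop-out turned out exactly as planned, the healthcare worker comparison would still be expected to fall short of the required sample.

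**Working it through.** **Inputs, all from the protocol article**
- Healthcare workers: 110 completers needed (55 per ward), 25% drop-out, ceiling 138 (section 2.2); 110 required for at least 80% power, level 0.05/9 = 0.0056 per test (section 3.3).
- Healthcare consumers: 150 completers needed, 10% non-completion, ceiling 165 (section 2.2).

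**1. Reproduce the stated targets**
- n × (1 + d): 110 × 1.25 = 137.5, rounded up to 138; 150 × 1.10 = 165. Both stated figures are matched.
- n / (1 − d): 110 / 0.75 = 146.7, rounded up to 147; 150 / 0.90 = 166.7, rounded up to 167. Neither stated figure is matched.
- Rounding up by ward gives 55 / 0.75 = 73.3, so 74 per ward and 148 in all.

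**2. Expected completers at the stated ceilings, N × (1 − d)**
- Healthcare workers: 138 × 0.75 = 103.5, or 51.75 per ward. Shortfall 110 − 103.5 = 6.5, about 6% of 110.
- Healthcare consumers: 165 × 0.90 = 148.5. Shortfall 1.5, or 1% of 150.

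**3. Loss rate that each ceiling can absorb, 1 − n / N**
- Healthcare workers: 1 − 110/138 = 20.3%. As a check, 138 × 0.80 = 110.4.
- Healthcare consumers: 1 − 150/165 = 9.1%.

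**4. Chance of reaching 110 healthcare worker completers** (binomial, independent losses, 75% retention)
- 138 recruited: P(X ≥ 110) = 0.118.
- 147 recruited: P(X ≥ 110) = 0.56. This is the fair comparator: correct inflation meets the target on average, not with certainty.

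**5. Effect on power (illustration only)**

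The protocol gives no effect size. Assume that 55 per ward gives exactly 80% power in a two-sided two-sample t-test.
- At level 0.0056 this implies a standardised difference of about 0.70. With 51.75 per ward, power is 76.7%.
- At level 0.05 the same exercise gives 77.5%.

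The loss is about 3 percentage points on either level.

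**The case against.** **The error is small in practice and sits in a secondary aim.** This is a two-ward, non-randomised feasibility pilot. Efficacy is assessed only if enough data are collected, the 25% is an estimate, and drop-out is one of the things the study sets out to learn. This stands, and it limits the weight of the point. It does not make the sentence correct.

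**The power loss rests on assumptions.** The t-test and the effect size are not in the document. The abstract and section 3.4 plan nonparametric tests, there are three time points, and section 3.3 says at least 80%, so 55 may carry some margin. This stands: the 77% is an illustration. The shortfall in completers does not depend on it.

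**Correct inflation would not secure the target either.** With 147 recruited, the chance of 110 completers is only about 56%. This stands, and it is a reason to soften the promise of completion whatever number is chosen. The contrast of 12% with 56% is still due to the inflation error.

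**The consumer figure hardly matters.** This stands. It is two people out of 167, in an exploratory part with no power claim resting on 150. Its use here is to confirm how both targets were formed.

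**A stronger reading to resist.** A reader might infer that, because recruitment, completion and drop-out rates are primary feasibility indicators, feasibility would be judged against a wrong target. Sections 1.2 and 3.1 list those rates but attach neither 138, 110 nor any other threshold to them, so the document does not support that inference.

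**Conclusion.** The healthcare worker target is wrong as written. At the plan's own 25% drop-out, a ceiling of 138 yields 103.5 expected completers (about 52 per ward) against the 110 that section 3.3 requires. It suffices only if drop-out is about 20% or less. The chance of reaching 110 is about 12%, assuming independent losses at 25%. No wording rescues the figure: 138 is a maximum, and those who discontinue are not analysed.

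The consequence is modest: about 3 points of power under the assumed t-test calibrated to exactly 80% at 55 per ward. The sentence should be corrected, but the error does not undermine the feasibility objective or invalidate the study. The consumer discrepancy is the same slip at negligible size.

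**What to change.** Any one of these reconciles the healthcare worker figures:
- Keep 138 and state about 103 expected completers (about 52 per ward), with the power in section 3.3 restated for that number and the effect size and test it assumes.
- Keep 138 and 110, and state that 138 allows for 20% drop-out.
- If the wards have the staff, raise the ceiling to 147, or 148 to give 74 per ward. The document gives no headcount, so whether this is attainable cannot be judged from it.

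In every case, say that the completers are expected rather than ensured. In the same edit, either raise the consumer ceiling from 165 to 167, or state 148 expected completers or an allowance of 9%.

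The first two options cost only a change of text and, for the first, a repeat of the power calculation. The third costs up to 9 or 10 more healthcare worker recruits (147 − 138 or 148 − 138). Raising the consumer ceiling costs 2.

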### 2.3. Procedure

*Recruitment*. To recruit healthcare worker participants, the research team will schedule face-to-face research presentations to nurses and medical professionals on their usual in-service education days. Posters will be placed in the ward areas and research team members will offer information on a one-to-one basis. The nurse managers will also be asked to send out advertisements to their team. Potential participants will be given the participant information sheet and invited to contact a member of the research team if still interested in participating. After the delivery of the intervention, healthcare worker participants from the intervention group will be invited to participate in focus group interviews via email from the research team and verbal invitations from nurse managers. To recruit healthcare consumer participants, advertisements on physical notice boards and table displays will be placed in ward areas. The research team will be present on the wards and invite healthcare consumers on a face-to-face basis to complete the surveys.

*Data collection.* Over the course of the study, quantitative and qualitative data will be gathered at different time points to collect a wide range and type of information for the feasibility and efficacy assessment of the EmpEd. First, surveys will be administered at three time points using Qualtrics software. Each HW participant will be given the survey links via email and will use a unique identifier code, chosen by them, to enter the survey at the commencement of each data collection time point. HC participants will be given a hardcopy to complete with optional assistance provided. Second, two focus groups with approximately 5–10 HW participants from the intervention group will be facilitated after the delivery of the intervention. A research team member, who will not partake in the delivery of the intervention, will organise and facilitate these focus groups to collect qualitative data about the quality and delivery of the programme from the participants’ perspective. The focus group interviews will be transcribed and analysed along with other qualitative data. Finally, during the intervention HW participants will be able to provide hard-copy written feedback about the weekly content of the EmpEd. Participants who discontinue or deviate from the protocol will be excluded from any analysis.

*Participant reimbursement.* To promote participant retention, remuneration for participation will be provided. Payment for each participant is not financially viable, thus financial remuneration is limited to prize draws (i.e., -100 NZD grocery vouchers) for HW participants. Everyone who signed up for the study automatically enters the prize draws. Members of the control group participate in three prize draws at each of the three quantitative data collection periods. The intervention group will enter only one prize draw at the end of the study. Healthcare consumers will receive no reward for participation.

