## Abstract

Empathy is positively related to healthcare workers and patients’ wellbeing. There is, however, limited research on the effects of empathy education delivered in acute clinical settings and its impact on healthcare consumers. This research tests the feasibility and the potential efficacy outcomes of an immersive education programme developed by the research team in collaboration with clinical partners and a multidisciplinary advisory group. Healthcare worker participants in the intervention ward will receive an 8-week immersive empathy education. The primary outcome (feasibility) will be assessed by evaluating the acceptability of the intervention and the estimated resources. The secondary outcome (efficacy) will be assessed using a quasi-experimental study design. Non-parametric tests will be used to test healthcare worker participants’ empathy, burnout, and organisational satisfaction (within-group and across groups), and healthcare consumer participants’ satisfaction (between-group) over time. Despite growing interest in the importance of empathy in professional relationships, to our knowledge, the present pilot study is the first to explore the feasibility and efficacy of an immersive empathy education in New Zealand. Our findings will provide critical evidence to support the development of a randomised cluster trial and potentially provide preliminary evidence for the effectiveness of this type of empathy education.

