### 1.2. Objectives

The primary objective of this pilot study is to evaluate the feasibility of the developed immersive Empathy Education Programme in the clinical setting. First, feasibility will be determined by assessing HWs’ acceptance of the intervention. Acceptability will be measured by five indicators: recruitment rates; completion rates; drop-out rates, HW participants’ written feedback; and their oral evaluation of the programme. Second, feasibility will be evaluated by estimating the programme costs and organisational resources needed to facilitate an EmpEd in the future including time commitment, material and financial resources required to run the programme. The secondary objective is to assess the efficacy of the proposed EmpEd. This secondary objective is dependent on the outcome of the feasibility assessment. That is, if the delivered EmpEd’s acceptance level enables us to collect data and ensure acceptable power for statistical analysis, then we will assess HWs’ level of empathy, subjective wellbeing, organisational satisfaction, and HCs’ satisfaction over time.

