## 2. Method

### 2.1. Design

This quasi-experimental study of healthcare workers and healthcare consumers is a feasibility and pilot study to form the basis for a future, prospective cluster randomised trial (CRT). The single centre study will be conducted at one tertiary hospital in New Zealand. To minimise harm to participants, the key characteristics that will guide the ward selection are stable workforce, predictable patient population, and stable leadership. Based on local conditions, the Chief Nursing Officer will identify and select two wards (intervention and control ward) that meet these criteria. Although everyone on the wards will be invited to participate in the study, it is reasonable to expect that not everyone would want to be enrolled in the research. Thus, the wards are the study setting, and the groups are the enrolled participants on the wards.

Participants will be pre-allocated into four groups. Based on the participants’ location in the hospital, they will be either part of the intervention or the control group. Based on the participants’ position in the healthcare system, they will be either part of the HW group or the HC group. Participants in the HW groups will be constant during the study, while participants in the HC groups will differ across time points. HWs in the intervention ward/group will receive an 8-week immersive empathy education programme and the control ward/group will operate as usual during the research study. HCs will receive care, support and will interact with healthcare workers as usual in both wards/groups. HCs in the intervention ward/group will not be directly affected by the intervention; however, they will experience limited exposure to the education programme (e.g., seeing educational materials on the ward walls).

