The study duration is expected to be approximately 30 weeks (see Figure 1 for the outline timetable for participants). The study will begin with a 3-week recruitment and consenting period prior to delivering the intervention. Baseline assessment of all participants will be continuous in this 3-week period (Weeks 1–3). This is followed by the 8-week intervention. The research team will deliver the immersion programme in the intervention ward, while the control ward will continue to operate as usual with no interaction/engagement during this time with the research team (Weeks 4–12). After delivering the intervention, all participants will complete the second assessment (Week 13–15). HWs in the intervention ward will be invited to participate in focus group interviews about their experiences of the EmpEd (initiation, Week 13; interviews, Weeks 16–17). Three months later, a final follow-up assessment of all participants will complete the quasi-experiment (Weeks 27–30). The design is adaptive in that the study duration and the intervention can be changed if participation and feedback from study participants indicate necessary adjustments for successful study continuation.

An advisory group will be established, and will be made up of health care professionals, healthcare consumer representatives, cultural advisors, and international experts in empathy education. The purpose of the advisory group is to ensure that relevant perspectives and voices are heard and considered in the design of the intervention and the assessment of the EmpEd (e.g., considering different value orientations in a multicultural environment, the work schedule of HW participants, and access to resources). Three advisory meetings will be held over the course of the programme, and a 100 NZD gift voucher per meeting will be offered to each advisor for their contribution.

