## 3. Measures and Outcomes

### 3.1. Feasibility Outcomes

The feasibility of a prospective CRT on enhancing empathy in the clinical setting will be estimated based on the acceptability of the intervention (1) and the estimated organisational resources needed to continue the programme (2). First, the acceptability of the intervention will be assessed both quantitatively and qualitatively: (a) analysing recruitment, completion, and drop-out rates; (b) monitoring active and passive participation in the intervention; (c) optional weekly written feedback from healthcare worker participants; (d) surveying healthcare worker participants about their prior expectations of the intervention and whether their expectations were met after the intervention; (e) and focus group interviews with approximately 5–10 healthcare worker participants. The main objective of the focus groups is to review and evaluate the EmpEd from the participants’ perspective: evaluation of quality and mode of delivery, usefulness, staff engagement, and specific components of the intervention. Second, to determine the resources needed by the organisation to run an EmpEd, the following need to be considered and estimated: (a) scientific personnel for EmpEd training and supervision; (b) clinical networks and cooperation; and (c) equipment and material costs. Importantly, the EmpEd programme review is not only to measure the feasibility, engagement, and applicability of the programme, but also to assess the viability of continuing aspects of the immersion programme, for example, regular mindfulness sessions or the hydration station.

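### The only described link between a healthcare worker's three surveys is a self-chosen code, so forgotten or changed codes may make responders look like drop-outs and remove them from within-group analysis

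*Protocol article*

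**What the plan says.** Section 2.3 states that "surveys will be administered at three time points using Qualtrics software". On delivery it says: "Each HW participant will be given the survey links via email". On identification it says that each of them "will use a unique identifier code, chosen by them, to enter the survey at the commencement of each data collection time point". The article names no other key joining one person's surveys and describes no prompt, reminder or recovery step for the code.

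Three other places make the link matter:

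- Section 2.1 describes a closed staff cohort: "Participants in the HW groups will be constant during the study". Healthcare consumers, by contrast, are different people at each time point. The same section says "The study duration is expected to be approximately 30 weeks" and places the assessments in Weeks 1–3, 13–15 and 27–30.
- Section 1.2, on the primary objective, says: "Acceptability will be measured by five indicators: recruitment rates; completion rates; drop-out rates", followed by written and oral feedback. Section 3.1 repeats this as "analysing recruitment, completion, and drop-out rates".
- The Abstract says that the staff outcomes will be tested "within-group and across groups" over time.

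**The concern.** A freely chosen code has to be reproduced about 12 weeks after it is first used, and again about 14 weeks after that. A participant who returns all three surveys but enters a different code at one of them leaves an incomplete record under the first code and an apparently new person under the second. At person level, that participant cannot readily be distinguished from someone who left.

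Two things are at stake. The first is the person-level drop-out rate. It is a primary feasibility indicator, and the Discussion intends to use what is learned about drop-out to improve the design of the cluster randomised trial. If failed links are mixed into it, the rate carried forward is too high. The second is the within-group analysis. Paired change can be computed only for people whose records match, so responders with unmatched codes contribute nothing to it.

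Timing adds to the case for acting now. Codes chosen at baseline cannot be repaired at Week 13 or Week 27 if no means of recovering them was set up.

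**Working it through.** **Inputs from the article.** Section 2.2: 25% expected drop-out, up to 138 staff recruited, 110 completers wanted (55 per ward). Section 2.1: three assessments, hence two follow-ups that must each be linked to baseline.

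**Input not in the article.** The probability *m* that a returning participant's code fails to match at a given follow-up. I assume 2%, 5% or 10%, independent between the two follow-ups and with no recovery.

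**The plan's own figure.** 110 × 1.25 = 137.5, which rounds up to the stated 138. But 25% drop-out from 138 leaves 138 × 0.75 = 103.5 completers. For 110 completers, 110 / 0.75 = 146.7, i.e. 147, would be needed. Conversely, 110 completers out of 138 means drop-out of 1 − 110/138 = 20.3%. This is a separate matter. It is noted here because it gives two possible starting points, and both are shown.

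**Formulas.** Linked across all three surveys = completers × (1 − *m*)². Apparent drop-out = 1 − linked/138.

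| Assumed failure per follow-up | Linked, from 103.5 completers | Apparent drop-out (true 25%) | Linked, from 110 completers | Apparent drop-out (true 20.3%) |
|---|---|---|---|---|
| 0% | 103.5 | 25.0% | 110 | 20.3% |
| 2% | 99.4 | 28.0% | 105.6 | 23.4% |
| 5% | 93.4 | 32.3% | 99.3 | 28.1% |
| 10% | 83.8 | 39.2% | 89.1 | 35.4% |

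Example for 5%: 103.5 × 0.95² = 103.5 × 0.9025 = 93.4, and 1 − 93.4/138 = 32.3%.

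**In people.** From 103.5 completers, those who responded throughout but cannot be linked number 103.5 − 99.4 = 4.1, 103.5 − 93.4 = 10.1 and 103.5 − 83.8 = 19.7 at the three rates.

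**One link only.** If an analysis needs only one follow-up linked to baseline, the factor is (1 − *m*). From 103.5 people, 101.4, 98.3 or 93.2 are linked, and apparent drop-out is 26.5%, 28.8% or 32.5%.

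**What does not depend on *m*.** The number of surveys returned at each wave can be set against the number enrolled without matching any code. A comparison of the two wards at one time point needs only the ward to be recorded on each return.

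The loss of power in the within-group tests cannot be derived, because section 3.3 gives no effect size, standard deviation or correlation over time.

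**The case against.** The strongest reply is that the article does not state the defect outright. It does not say that the code is the only key, that no list of codes against email addresses is kept, or that participants must rely on memory. Staff give written consent and are emailed their links, so the team knows who is enrolled, and a condensed article may leave code storage and recovery to the full protocol. The code is called unique and is used to enter the survey. If entry is checked against registered codes, a typing error would be caught at once and duplicates refused. Nowhere is an unmatched code said to count as a drop-out, and a surplus of new codes at a later wave would itself reveal failed links. The failure rates are assumed, and at 2% the effect is small. Finally, staff report burnout, secondary trauma and views of their own unit, and nurse managers help with recruitment. A self-chosen code may be a deliberate protection that supports candour and participation.

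Most of this stands, and it limits the point. A reader might infer that staff are tracked by nothing but this code, that mismatches will certainly be counted as drop-outs, and that the primary outcome is therefore biased. The article supports none of these as a certainty.

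Two things remain. The freely chosen code is a stated procedure, so criticising it is not a complaint about missing detail. And totals per wave do not show who completed all three surveys or who missed one, so person-level drop-out and paired change stay exposed. The confidentiality argument weighs against identifiable links, but not against a code that stays anonymous and can be regenerated.

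**Conclusion.** The concern holds as a data-linkage risk, not as a demonstrated error. The only link described is a code each participant chooses and enters three times over about 30 weeks. Failures of that code may inflate person-level drop-out and shrink the within-group sample. They need not affect returns per wave or between-ward comparisons at one time point.

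The size is unknown. With the planned 25% true drop-out, apparent drop-out would be about 28%, 32% or 39% at an assumed 2%, 5% or 10% failure per follow-up. This rests on independent failures at the two follow-ups, no recovery, and unmatched people being counted as lost. With working recovery, or codes checked at entry, the inflation would be smaller and could vanish.

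Two further readings are tempting but unsupported. Section 2.3 excludes participants who discontinue from any analysis, so a reader might infer that unmatched responders would be dropped from the between-ward comparisons too. The article does not say that an unmatched code is treated as discontinuation. A reader might also infer that codes will fail more often in the control ward, which has no contact with the team during the intervention. The unequal contact is stated, but nothing shows a difference in code failure.

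**What to change.** Before baseline:

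1. Replace the free choice with a code built from a few fixed personal facts that do not change and that the participant can regenerate at each survey. This keeps responses anonymous to the team and removes the need to remember a code.
2. Alternatively, if the confidentiality cost is judged acceptable, send individual survey links carrying a study identifier. A team member who does not deliver the programme would hold the key, apart from the responses. Section 2.3 already uses such a person for the focus groups.
3. Under either option, record the ward on each return, count completion per wave from returns against the enrolled list, and report unlinked returns as a category separate from drop-outs.

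The cost of the first option is a few extra code questions and a small residual number of duplicate or unmatched codes, which the third step makes visible. The second option removes recall entirely but makes sensitive staff data traceable through the key. That could affect recruitment, itself a primary indicator, so the first is the safer default.
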